**1**

**1. Protocol Summary**

**1.1 Synopsis**

**Title:**

A prospective case series of subcutaneous immunoglobulin for prophylaxis of infections in patients with chronic lymphocytic leukemia with impaired humoral immunity

**Study Description:**

Patients with chronic lymphocytic leukemia (CLL) are at increased risk of infections as compared to age matched controls, with infections being a major cause of morbidity and mortality. Previous studies have shown that patients with CLL have both hypogammaglobinemia and impaired humoral immunity as defined by vaccine responses to both polysaccharide and peptide antigens. Attempts at decreasing infections in CLL have included therapy with prophylactic antibiotics and intravenous immunoglobulin. In general clinical practice and in previous studies, patients have started IV immunoglobulin replacement therapy if they have a history of serious infection or hypogammaglobinemia (defined as IgG below 400 g/dL), but vaccine responses have not been evaluated. This study will identify CLL patients with humoral immunodeficiency by checking both Ig levels and vaccines responses. In patients with impaired humoral immunity, we will use subcutaneous immunoglobulin replacement to show this intervention will increase Ig levels, protective antibody titers, and be well tolerated.

**Objectives:**

*Primary objective:*

To identify patients with CLL with humoral immunodeficiency despite serum IgG ≥ 400 mg/dL

*Secondary objectives:*

1. Efficacy of subcutaneous Ig replacement therapy in increasing Ig levels

2. Efficacy of subcutaneous Ig replacement therapy in increasing protective antibody titers for diphtheria, tetanus, streptococcus pneumoniae

3. Safety and tolerability of subcutaneous Ig replacement therapy

4. Quality of life (SF 36) on subcutaneous Ig replacement therapy

5. Track the number of infections requiring antibiotics, further characterized per severity as defined in previous studies.

**Endpoints:**

1. Identify patients with CLL with humoral immunodeficiency despite serum IgG ≥400 mg/dL.

2. Demonstrate efficacy of subcutaneous Ig replacement therapy in increasing Ig levels and protective antibody titers.

**Study Population:**

*Sample size:*

From previous literature, we expect to evaluate 20-30 patients for secondary immunodeficiency to reach a goal of 10 patients to undergo treatment with subcutaneous immunotherapy.

*Gender:*

Both males and females will be enrolled in this study.

*Age:*

Eligible patients will be ages 18 and above.

*General health status:*

All patients with CLL who are medically stable with an expected survival of > 1 year per their primary hematologist/oncologist will be offered enrollment in this study.

*Geographic area:*

Patients will be recruited from hematology/oncology practices in Rochester, NY. The majority of patients will come from the CLL Registry and Rochester Regional Health, which includes over 300 patients. Other local hematology/oncology practices may also contribute patients to the study.

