**5.5 Strategies for Recruitment and Retention**

The study will largely recruit from the hematology/oncology division at Rochester Regional Health. The majority of active CLL patients are enrolled in a registry, which will aid in identifying potential subjects. The registry has roughly 300-350 patients with CLL. Additionally, through professional networks and relationships, the study will also be advertised to other local hematology/oncology practices, each of whom have contributed patients in the past to previous research studies. In total, we expect to evaluate 20-30 patients to have 10 qualify for the therapy portion of the study with subcutaneous Ig replacement.

Once enrolled, subjects will be in close contact with the investigators and the clinical research support staff regarding the results of their laboratory evaluation, and if applicable, the administration of subcutaneous Ig replacement. For subjects being treated with subcutaneous Ig replacement, the first 2-3 visits will be done on site with the clinical research coordinator. If and when subjects are comfortable self-administering subcutaneous Ig therapy at home, the clinical research coordinator will be in phone contact at fixed intervals regarding tolerability of therapy. Subjects will also be asked to pick up supplies for Ig replacement on a monthly basis from the clinical research coordinator.

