**8. Study Assessments and Procedures**

**8.1 Efficacy Assessments**

Efficacy will be assessed by the study drug increasing immunoglobulin levels, tetanus, diphtheria, and pneumococcal IgG levels, and study drug safety and tolerability in this population.

The secondary endpoint of quality of life will be assessed by the SF-36 quality of life assessment (please see attachment), which is a validated questionnaire. This will be administered monthly by the study coordinator.

The secondary endpoint of the frequency of humoral deficiency in patients with chronic lymphocytic leukemia will be assessed with the following laboratory data:

- IgG, IgM, IgA, IgE, CD4, CD8, CD3, and CD19 lymphocyte subsets
- Pre and post vaccine IgG responses 4 weeks apart to the following antigens: *Streptococcus pneumoniae*, diphtheria, tetanus, with a normal response defined as followed:
  - Strep pneumoniae (based on response to PPV):
    - If < 1.3, need to increase 2 fold to above 1.3 OR increase 4 fold
    - If > 1.3, need to increase 2 fold
    - Responses need to be demonstrated by 70% of serotypes
  - Diphtheria, normal response
    - 2 fold increase into protective range
  - Tetanus, normal response
    - 2 fold increase into protective range

Impaired vaccine response defined at abnormal response to any of the above antigens.

All blood specimens will be handled processed at the Rochester Regional Health laboratories as per usual clinical care. Laboratory data will be provided and explained to study subjects upon request.

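### The frequency of humoral deficiency would come from a volunteer and referral sample, because the protocol does not say who is approached and requires no count of those approached or declining

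*Protocol*

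**What the plan says.** The primary objective in the synopsis is "To identify patients with CLL with humoral immunodeficiency despite serum IgG ≥ 400 mg/dL". Section 3 repeats it, and section 9.4.2 gives it a descriptive analysis. Section 8.1 refers to "The secondary endpoint of the frequency of humoral deficiency in patients with chronic lymphocytic leukemia" and assesses it with the same immunoglobulin, lymphocyte-subset and vaccine-response work-up that section 3 uses for the primary objective.

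On who enters, the synopsis (Study Population) says that all CLL patients "who are medically stable with an expected survival of > 1 year per their primary hematologist/oncologist will be offered enrollment", and that "we expect to evaluate 20-30 patients for secondary immunodeficiency to reach a goal of 10 patients" for treatment. Section 5.5 adds: "The registry has roughly 300-350 patients with CLL", and "the study will also be advertised to other local hematology/oncology practices". The synopsis expects most patients to come from the registry, while other practices may contribute some.

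Section 5.2 excludes patients on immunoglobulin replacement and those with IgG below 400 mg/dL. Section 5.4 states that there will be no screen failures and keeps patients with a normal evaluation in the study. Section 4.1, on minimizing bias, mentions laboratory endpoints and a validated questionnaire; it does not mention selection of patients.

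**The concern.** A frequency needs a numerator, a denominator and a known route into the denominator. The first two exist, because every evaluated patient is classified and those with a normal result are retained. The third does not. Several hundred patients may be offered a place, 20-30 are expected to be evaluated, and nothing fixes which ones.

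The treatment on offer is infection prophylaxis, and section 2.2 reports that low pneumococcal titers track infection risk more closely than serum IgG does. Willingness to join, or an oncologist's readiness to refer, could therefore be related to the condition being counted. If so, the proportion would reflect how patients came in as well as how common the deficiency is.

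At stake is the reading of a stated endpoint. Section 4.2 hopes for larger controlled studies, and their screening numbers could rest on this proportion. Who was approached and who declined can only be recorded reliably as it happens.

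**Working it through.** **The plan's own figures.** The schema (section 1.2) expects 10 abnormal and 10-20 normal evaluations.
- Evaluated: 10 + 10 = 20 to 10 + 20 = 30, which reproduces the stated 20-30.
- Implied frequency: 10/30 = 33% to 10/20 = 50%.

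This checks internal consistency only. The protocol gives no rate from the literature from which to derive it.

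**Share of the registry evaluated** (sizes from section 5.5).
- Registry of 300: 20/300 = 6.7% to 30/300 = 10.0%.
- Registry of 350: 20/350 = 5.7% to 30/350 = 8.6%.

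These are upper limits, since any patient from another practice takes a place from the registry.

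**Sampling error alone** (exact Clopper-Pearson 95% interval).
- 10/20: 27% to 73%.
- 10/30: 17% to 53%.

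**Illustration 1: selection through infection history.** All inputs are assumptions: 25% of patients are infection-prone with 60% impaired, and the rest are 30% impaired. The true frequency is 0.25 × 0.60 + 0.75 × 0.30 = 37.5%. If infection-prone patients enroll at k times the rate of others, their share of the sample is s = 0.25k / (0.25k + 0.75), and the expected observed frequency is 0.60s + 0.30(1 − s).
- k = 2: s = 0.40, observed 42%.
- k = 3: s = 0.50, observed 45%.
- k = 5: s = 0.625, observed 49%.

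At k = 3 the shift is 7.5 points. The standard error with 30 patients is √(0.375 × 0.625 / 30) = 8.8 points.

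**Illustration 2: selection directly on impairment.** Let R be the assumed ratio of participation probability, impaired to not impaired. The observed frequency is pR / (pR + 1 − p).
- p = 33%: 43%, 50% and 60% at R = 1.5, 2 and 3.
- p = 50%: 60%, 67% and 75% at the same values.
- In the other direction, R = 0.5: p = 1/3 gives 0.1667 / (0.1667 + 0.6667) = 20%, and p = 1/2 gives 0.25 / (0.25 + 0.5) = 33%.

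A ratio of 2 moves a true 33% across the whole of the plan's implied range. A ratio of one half moves a true 50% back across it. The documents say nothing on which ratio applies.

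**Stopping at 10.** If screening ended exactly at the tenth impaired patient, 10/N would average 35.6% for a true 33.3% and 52.5% for a true 50% (negative binomial expectation), an upward shift of about 2 points. This is separate from selection and small beside the sampling error.

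**The case against.** The strongest reply is that the study calls itself a single-center case series (section 4.1) and a proof of concept (section 9.2), with descriptive statistics throughout, and never claims a representative prevalence. To show that impaired patients with IgG of at least 400 mg/dL exist, a volunteer sample is enough. That stands, and it limits the weight of the point. It does not remove it, because section 8.1 names a frequency and gives its target as patients with CLL.

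Three stronger readings are tempting, and the protocol does not support them.

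- **That a frequency is the main result.** The primary objective is to identify patients, and the hypothesis in section 9.1 can be read as a claim of existence. The only explicit frequency is labelled secondary.
- **That the study takes the first 20-30 responders.** No section says so. The number is an expectation driven by the goal of 10 treated patients, and the order of approach is left open.
- **That the frequency will be too high.** Infection-prone patients may be keener to join. But section 2.2 says that patients with serious infection or low IgG are commonly started on immunoglobulin, and section 5.2 excludes those on replacement or with IgG below 400 mg/dL. The requirement for medical stability may also favor fitter patients.

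Two further replies are fair. A recruitment log may be kept outside the protocol, so silence does not prove that decliners will go uncounted; the protocol simply does not require it. And random-order invitation does not remove selection by refusal.

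**Conclusion.** The point holds as an inexpensive improvement. No figure in the protocol is wrong. The plan names a frequency in CLL patients as an endpoint but has no rule for who is approached, so the result would describe a volunteer and referral sample of at most about 10% of the registry. If those approached and declining are not recorded, no later analysis can show how far that sample departs from the eligible patients.

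The direction and size of any bias cannot be derived from the documents. The 42%-49% against a true 37.5% rests wholly on assumed infection-prone share, impairment rates and enrollment ratios. With 20-30 patients, sampling error is already wide (17%-53% for 10 of 30), and the central illustrated shift of 7.5 points is smaller than one standard error.

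**What to change.** In the synopsis (section 1.1, Study Population) and section 5.5, state that eligible registry patients are approached in random order, or that consecutive clinic attenders are approached from a fixed date, until the therapy group is full.

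Keep a log by source (registry or other practice) of the numbers approached, ineligible (with IgG below 400 mg/dL counted separately), declining and evaluated.

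Report the frequency among evaluated patients with IgG of at least 400 mg/dL, with an exact interval. Show registry-approached patients separately from those referred by other practices, who may still be evaluated and treated. State beside the result that screening ended when the therapy group was full, that refusal can still select patients, and that the result is from a single-center case series.

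The cost is a few sentences of protocol text and a log. The ordered approach removes selection by referral and by speed of response, but not by refusal. The downside is that recruitment may be slower and the yield of impaired patients lower than with an open offer. Showing patients by source also splits an already small denominator.

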**Phase:**

Phase 2

**Description of Sites and Enrollment:**

This is a single center study. Patients will be recruited from hematology/oncology practices in Rochester, NY. The majority of patients will come from the CLL Registry and Rochester Regional Health, which includes over 300 patients. Other local hematology/oncology practices may also contribute patients to the study. All patients will be evaluated at the allergy/immunology office at Rochester Regional Health.

**Description of Study Intervention:**

Patients with humoral immunodeficiency will receive subcutaneous immunoglobulin replacement (Hizentra 100 mg/kg/week).

**Study Duration:**

We expect to enroll 10 subjects for the therapy phase of the study within 1 year. Each subject will undergo evaluation for humoral immunodeficiency over a 4-week period. Patients with abnormal evaluation will be treated with 6 months (24 weeks) of subcutaneous Ig replacement therapy, followed by a 3 month (12 week) wash out period, for a total study duration of 10 months (40 weeks). We plan to complete all study visits and analyze data within two years of when enrollment starts.

**Participant Duration:**

The entirety of the study will entail 10 months (40 weeks) for each subject:

4 weeks of laboratory evaluation

24 weeks of subcutaneous Ig replacement

12 weeks of wash out period

**1.2 Schema**

Please see below.

Screening subjects for humoral immunodeficiency (n = 20-30)

4 weeks

Normal evaluation (n = 10-20) Abnormal evaluation (n=10)

No further intervention Subcutaneous Ig replacement

24 weeks weeks

Discontinue Ig replacement

12 weeks

Final lab evaluation

**1.3 Schedule of Activities**

Please see below.

|  | Screening | | Therapy with Ig Replacement | | | | | | | | | Wash Out Period | | | |
| --- | --- | --- | --- | --- | --- | --- | --- | --- | --- | --- | --- | --- | --- | --- | --- |
| Study visit | V1 |  | V2 | V3 | V4 | V5 | V6 | V7 | V8 | V9 | V10 | V11 | V12 | V13 | V14 |
| Week of study |  |  | 1 | 2 | 3 | 4 | 8 | 12 | 16 | 20 | 24 | 28 | 32 | 36 | 40 |
| Consent | X |  |  |  |  |  |  |  |  |  |  |  |  |  |  |
| Urine pregnancy test* | X |  |  |  |  |  |  |  |  |  |  |  |  |  |  |
| Medical history |  |  | X | X | X | X | X | X | X | X | X | X | X | X | X |
| Vitals |  |  | X | X | X | X | X | X | X | X | X | X | X | X | X |
| Physical exam |  |  | X | X | X | X | X | X | X | X | X | X | X | X | X |
| QoL (SF 36 form) |  |  | X | X | X | X | X | X | X | X | X | X | X | X | X |
| Pt teaching for Ig |  |  | X | X | X |  |  |  |  |  |  |  |  |  |  |
| Dispense study Ig |  |  |  |  |  | X | X | X | X | X | X |  |  |  |  |
| Pneumovax (PPV23) | X |  |  |  |  |  |  |  |  |  |  |  |  | X |  |
| Tetanus/diphtheria | X |  |  |  |  |  |  |  |  |  |  |  |  | X |  |
| IgG | X | X |  |  |  | X |  | X |  |  | X |  |  | X | X |
| IgM | X | X |  |  |  | X |  | X |  |  | X |  |  | X | X |
| IgA | X | X |  |  |  | X |  | X |  |  | X |  |  | X | X |
| IgE | X | X |  |  |  | X |  | X |  |  | X |  |  | X | X |
| IgG for 23 serotypes of strep pneumo | X | X |  |  |  | X |  | X |  |  | X |  |  | X | X |
| IgG for diphtheria | X | X |  |  |  | X |  | X |  |  | X |  |  | X | X |
| IgG for tetanus | X | X |  |  |  | X |  | X |  |  | X |  |  | X | X |
| T and B cell panel | X |  |  |  |  |  |  |  |  |  |  |  |  | X |  |

* Will be completed in women of child bearing age

**2. Introduction**

**2.1 Study Rationale**

Patients with CLL are at increased risk of infections as compared to age matched controls, with infections being a major cause of morbidity and mortality. Previous studies have shown that patients with CLL have both hypogammaglobinemia and impaired humoral immunity as defined by vaccine responses to both polysaccharide and peptide antigens. Attempts at decreasing infections in CLL have included therapy with prophylactic antibiotics and intravenous immunoglobulin. In general clinical practice and in previous studies, patients have started IV immunoglobulin replacement therapy if they have a history of serious infection or hypogammaglobinemia (defined as IgG below 400 g/dL), but vaccine responses have not been routinely evaluated. This study will provide a novel approach to identifying CLL patients with humoral immunodeficiency by checking both Ig levels and vaccine responses. In patients with impaired humoral immunity, we will use subcutaneous immunoglobulin replacement to show this intervention will be well tolerated and increase Ig levels and protective antibody titers.

**2.2 Background**

Lymphoproliferative disorders (LPD) are one of the most common hematologic malignancies. Each year in the U.S., approximately 15,000 patients are diagnosed with chronic lymphocytic leukemia (CLL). [1] Patients with CLL are at increased risk of infections as compared to age matched controls. [2] Furthermore, infections remain a major cause of morbidity and mortality, with up to 17% to 50% of infections being fatal. [2-4] Infection type and occurrence in CLL are related to disease stage and treatment history. CLL carries a known increased risk of bacterial infections, but certain anti-neoplastic agents increase the risk of viral infections, while the Bruton kinase inhibitor ibrutinib may decrease rates of infection. [5] Attempts at decreasing infections in CLL have included therapy with prophylactic antibiotics and intravenous immunoglobulin. In general clinical practice and in previous studies, patients have started immunoglobulin replacement therapy if they have a history of serious infection or hypogammaglobinemia (defined as IgG below 400 g/dL). [4-8] Immunoglobulin replacement therapy has been shown to decrease rates of bacterial infection in some studies, but the utility of the universal application of the practice remains unclear. A Cochrane meta-analysis concluded that the use of IVIG may be considered in patients with LPD with hypogammaglobinemia and recurrent infection, but acknowledged that the studies are heterogeneous. [9]

Previous studies have shown that patients with CLL have impaired humoral immunity as defined by vaccines responses to both polysaccharide and peptide antigens. [9] Patients with primary immunodeficiency are routinely evaluated for their humoral antibody response before immunoglobulin replacement is considered. However, the practice of checking vaccine responses prior to starting immunoglobulin replacement has been advocated, but not extensively studied in patients with CLL. [5, 10-12] Previous data has shown that low titers to pneumococcal vaccination was more highly associated with risk of infection as compared to serum IgG. [13] Thus, an immune evaluation including vaccine titers may help to identify CLL patients most at risk for life threatening infection as compared to patients with hypogammaglobinemia but preserved humoral immunity or patients with clinical infections alone with preserved immunoglobulin levels and function. Patients with impaired humoral immunity may benefit most from immunoglobulin prophylaxis.

Previous trials and clinical practice have used intravenous immunoglobulin in patients with CLL with recurrent infections and hypogammaglobinemia. [6, 8, 14] As compared to subcutaneous immunoglobulin, intravenous immunoglobulin carries a higher risk of an infusion reaction (including aseptic meningitis), renal dysfunction, theoretical risk of hypercoagulability, along with the need for trained medical personnel to provide intravenous access. [15, 16] Subcutaneous immunoglobulin mitigates these risks and can also be administered at home, providing much greater patient autonomy. [16-18] There is limited data on the use of SCIG in patients with secondary immunodeficiency and CLL, but one center has published experience with SCIG in lymphoproliferative diseases, including 21 patients with CLL. [19] A recent randomized study evaluated the use of SCIG in 24/46 patients with multiple myeloma, but did not detail the immune evaluation. [20]

This study is novel in that it will stratify patients with CLL according to their humoral response to peptide and polysaccharide vaccines, and will employ subcutaneous immunoglobulin replacement in those with an impaired humoral response.

**2.3 Risk/Benefit Assessment**

**2.3.1 Known Potential Risks**

- Immediate risks for the initial laboratory evaluation include the risks associated with phlebotomy (pain, bleeding, infection). For patients with humoral immunodeficiency who will be treated with subcutaneous Ig replacement with Hizentra, please see the package insert for potential risks.
- The investigators cannot identify any long term risks with this study beyond the risks associated with Hizentra, which are covered in the package insert.

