**2.3.3 Assessment of Potential Risks and Benefits**

Subcutaneous Ig replacement therapy with Hizentra is generally well tolerated by patients with primary immunodeficiency, and generally has a better safety profile as compared to IV Ig replacement therapy. In the opinion of the investigators, the nominal risks of a laboratory evaluation followed by therapy with Hizentra are outweighed by the benefits of identification of humoral immunodeficiency in patients who otherwise remain undiagnosed. Identification of these patents will lead to therapy with subcutaneous Ig replacement, which may decrease the risk of non-neutropenic infection and potentially improve quality of life.

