**7. Study intervention discontinuation and participant discontinuation/withdrawal**

**7.1 Discontinuation of Study Intervention**

Study intervention will also halt if patients experience a hypersensitivity reaction to the study drug. The study intervention will also be halted if there is any serious adverse event deemed related to the study drug by the study investigators. If the study intervention is halted, then pre and post vaccination titers will be obtained after subcutaneous immunoglobulin has been discontinued for 3 months. Infections will continue to be tracked through patient contact, the electronic medical record, and pharmacy data. Quality of life data will still be tracked through patient contact.

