**8.3.3.2 Relationship to Study Intervention**

The investigator will assess the relationship between the AE and the study drug. All AEs will be classified as either related or not related to the study drug.

Related: The AE is known to occur with the study intervention, there is a reasonable possibility that the study intervention caused the AE, or there is a temporal relationship between the study intervention and event. Reasonable possibility means that there is evidence to suggest a causal relationship between the study intervention and the AE.

Not Related – There is not a reasonable possibility that the administration of the study intervention caused the event, there is no temporal relationship between the study intervention and event onset, or an alternate etiology has been established.

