**8.3.5 Adverse Event Reporting**

At each clinical evaluation, the investigator or delegate will determine if any AEs have occurred. These will be recorded in a case report form. A medical diagnosis will be written if known. The investigator will follow the course of the AE.

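### The risk sections leave out the two study vaccines, and patients with a normal evaluation have no scheduled adverse event assessment after receiving them

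*Protocol*

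**What the plan says.** On risk, protocol section 2.3.1 states "Immediate risks for the initial laboratory evaluation include the risks associated with phlebotomy (pain, bleeding, infection". It refers the reader to the package insert for Hizentra and then adds: "The investigators cannot identify any long term risks with this study beyond the risks associated with Hizentra, which are covered in the package insert". Section 2.3.3 concludes that "the nominal risks of a laboratory evaluation followed by therapy with Hizentra are outweighed by the benefits". Neither section mentions vaccination.

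On procedures, the vaccine row of the section 1.3 schedule opens "Pneumovax (PPV23) | X", with the first mark under V1 and a second under V13 (week 36). The tetanus/diphtheria row has the same two marks. Section 3 makes titres before and after vaccination, 4 weeks apart, the basis for classifying humoral immunity.

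On adverse events, section 8.3.4 starts collection at written consent and ends it at an end of study visit. Section 8.3.5 says how events are found: "At each clinical evaluation, the investigator or delegate will determine if any AEs have occurred". Under section 4.4 a patient with a normal immune evaluation has completed the study.

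On later vaccination, section 7.1 says of patients whose treatment is halted that "pre and post vaccination titers will be obtained after subcutaneous immunoglobulin has been discontinued for 3 months". Section 7.2 lets the investigator withdraw a subject for safety, including for an adverse event.

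**The concern.** Vaccination is the one active procedure that every participant undergoes, and the primary objective cannot be assessed without it. A risk section that presents screening as blood sampling does not describe what the trial does to the patients who never receive study drug. For them, vaccination is the main exposure.

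The collection rule and the schedule also do not meet. The protocol promises adverse event capture from consent for everyone, but the visits at which events are elicited exist only for treated patients. Non-serious vaccine reactions in patients with a normal evaluation would then be known only if volunteered. Enquiry would also be unequal: patients with an abnormal evaluation are asked at V2 about the weeks since V1, and the others are not. Any summary of events in the screening phase would come mainly from one of the two groups.

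**Working it through.** This is a comparison of passages with one count.

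**Step 1: where the marks fall in the section 1.3 schedule.**

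| Item | Columns marked |
| --- | --- |
| Pneumovax | V1, V13 |
| Tetanus/diphtheria vaccine | V1, V13 |
| Serum IgG | V1, the unnumbered post-vaccine column, V5, V7, V10, V13, V14 |
| Medical history, vitals, physical exam | V2 to V14 only |

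**Step 2: risks named against procedures scheduled.** Sections 2.3.1 and 2.3.3 name phlebotomy or laboratory evaluation, and Hizentra. The schedule contains phlebotomy, Hizentra and two vaccines. No section of the protocol as shown names a vaccine risk.

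**Step 3: path of a patient with a normal evaluation.** Consent, vaccines and the first blood draw fall at V1. The second draw, 4 weeks later, is in a column with no visit number and laboratory tests only. The patient is then complete under section 4.4. Section 8.2 calls for vital signs and an examination at each study visit, but the only numbered visit for this patient is V1. A question asked there, on the day of vaccination, cannot capture a reaction that develops afterwards. The end of study visit that closes the window in section 8.3.4 is not in the schedule for this patient.

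**Step 4: path of a treated patient.** V2 follows the post-vaccine draw and includes history and examination, so reactions to the V1 vaccines can be elicited there. V14 (week 40) comes 40 − 36 = 4 weeks after the V13 vaccines and also includes history and examination. The gap in assessment is therefore confined to patients who do not enter treatment.

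**Step 5: how many patients.** The schema in section 1.2 gives 20 to 30 screened, 10 abnormal and 10 to 20 normal. The subtraction reproduces its figures:

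- 20 − 10 = 10 normal; 10/20 = 50%
- 30 − 10 = 20 normal; 20/30 = 67%

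**The case against.** The strongest reply is that the protocol does more for these patients than the schedule alone suggests, and much of that stands.

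- **Recording.** A reader might infer that vaccine reactions are not recorded at all. The documents do not support this. Section 8.3.4 opens the window at consent, sends local and systemic reactions to the case report form with time of onset, and counts events that surface at interviews or when a patient seeks care. Section 8.2 tracks serious events monthly, and section 8.3.6 requires them to be reported within 24 hours whatever the cause. Section 5.5 promises close contact about results. What is missing is a scheduled enquiry about non-serious reactions.
- **Attribution.** Section 8.3.3.2 says "All AEs will be classified as either related or not related to the study drug", and a reader might infer that vaccine reactions have no category. But the not-related class covers events with an established alternative cause, and a vaccine can be one. Calling a V1 reaction unrelated to a drug not yet given is correct. A separate vaccine-causality field is not needed.
- **Tolerability of the drug.** A reader might infer that vaccine reactions blur this result. The vaccines come about 4 weeks before the first infusion and, at V13, 36 − 24 = 12 weeks after treatment ends. With onset recorded, no mechanism for blurring is shown.
- **V14.** No new question is needed there, because history and examination are already scheduled.
- **Repeat vaccination.** A reader might infer that a patient who reacted at V1 is vaccinated again regardless. No section says so, and section 7.2 allows withdrawal for safety. The protocol does not, however, connect section 7.2 to the V13 vaccines or to the vaccination titres in section 7.1.
- **Consent.** Section 2.3.1 uses the word include, so its list need not be exhaustive, and the consent pages are not shown. Nothing can be concluded about what patients are told. The point concerns the protocol's own risk statement, which still omits a scheduled procedure.

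It may also be said that the schedule has no adverse event row at any visit, so its absence from the post-vaccine column proves little. That is fair, but section 8.3.5 ties the enquiry to clinical evaluations, and the schedule gives patients with a normal evaluation none after vaccination.

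**Conclusion.** The point holds in two parts. Sections 2.3.1 and 2.3.3 misdescribe screening by leaving out two vaccines that the schedule gives to every patient at V1 and to treated patients again at V13. And 50% to 67% of participants (10 of 20 to 20 of 30) have no scheduled adverse event assessment after vaccination, although section 8.3.4 promises collection through an end of study visit.

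The count assumes that everyone in the schema's 20 to 30 is vaccinated at V1 and that all 10 with an abnormal evaluation enter treatment. The severity is minor: the analysis is descriptive, the safety objective concerns subcutaneous immunoglobulin, serious events remain reportable, and no primary or secondary result is shown to change. It is worth correcting because it bears on patient safety, changes what the trial collects and needs no new visit.

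**What to change.** 1. In section 2.3.1, name vaccination at V1 and V13 among the study risks. In section 2.3.3, include it in the weighing of risk and benefit.
2. In section 1.3, mark an adverse event enquiry, covering vaccine reactions, for all patients at the existing 4-week post-vaccine draw. State in sections 4.4 and 8.3.4 that this contact closes adverse event collection for patients with a normal evaluation.
3. Reconcile the V13 vaccinations and the vaccination titres in section 7.1 with the withdrawal provision in section 7.2 for a patient who reacted at V1. What the clinical rule should be is for the sponsor and investigators; none is proposed here.

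The cost is protocol wording, one question on the case report form at a blood draw that already takes place, and a few more non-serious events to record.
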